## Abstract

**Background:**

In comparison to other Europe countries, Dutch adolescents are at the top in drinking frequency and binge drinking. A total of 75% of the Dutch 12 to 16 year olds who drink alcohol also engage in binge drinking. A prevention programme called Preventure was developed in Canada to prevent adolescents from binge drinking. This article describes a study that aims to assess the effects of this selective school-based prevention programme in the Netherlands.

**Methods:**

A randomized controlled trial is being conducted among 13 to 15-year-old adolescents in secondary schools. Schools were randomly assigned to the intervention and control conditions. The intervention condition consisted of two 90 minute group sessions, carried out at the participants' schools and provided by a qualified counsellor and a co-facilitator. The intervention targeted young adolescents who demonstrated personality risk for alcohol abuse. The group sessions were adapted to four personality profiles. The control condition received no further intervention above the standard substance use education sessions provided in the Dutch national curriculum. The primary outcomes will be the percentage reduction in binge drinking, weekly drinking and drinking-related problems after three specified time periods. A screening survey collected data by means of an Internet questionnaire. Students have completed, or will complete, a post-treatment survey after 2, 6, and 12 months, also by means of an online questionnaire.

**Discussion:**

This study protocol presents the design and current implementation of a randomized controlled trial to evaluate the effectiveness of a selective alcohol prevention programme. We expect that a significantly lower number of adolescents will binge drink, drink weekly, and have drinking-related problems in the intervention condition compared to the control condition, as a result of this intervention.

**Trial registration:**

This trial is registered in the Dutch Trial Register (Cochrane Collaboration) as NTR1920.

## Background

Binge drinking is an increasing problem among young adolescents in the Netherlands. The recent use of alcohol among pupils in secondary education (12 to 16 years of age) in the Netherlands is declining, while binge drinking among these pupils is increasing. Nowadays, 75% of the Dutch 12 to 16 year olds who drink alcohol also engage in binge drinking [1]; this implies consuming five or more alcoholic drinks on one occasion in the past month. The largest proportion of binge drinkers are found in the age category of 15 and 16 years old. In comparison to other European countries, Dutch adolescents are among the leaders in drinking frequency and binge drinking [2,3].

In adolescents, heavy alcohol consumption is associated with premature and violent deaths, e.g. traffic accidents, having risky sexual intercourse [4,5] and poor academic performance, learning difficulties and school dropout [6-8]. In addition, heavy alcohol use during puberty appears to be related to damage to the development of cognitive and emotional abilities [9,10] and an elevated risk of later dependence and misuse [11,12]. Alcohol-related risks to cognitive functions seem to be higher in adolescents than in adults [11]. From the point of view of public health, prevention of heavy alcohol use among adolescents is essential.

There is little scientific evidence that universal prevention programmes aimed at youngsters affect drinking behaviour. Recent meta-analyses show that such programmes have small or no effects on alcohol use and binge drinking [3,13,14]. Exceptions to this are interventions aimed at both adolescents and their parents [15] and integrated programmes with multiple years of intervention and professional support [13,16,17]. Meta-analyses of school-based substance use prevention programmes have concluded that selective prevention programmes, targeting populations at increased risk, generally yield higher effects than universal programmes (e.g. [13,18]). According to Cuijpers and colleagues [13], selective prevention programmes have proved effective, but the availability of these programmes is limited. Therefore there is a recognized need in the field of substance use prevention for selective prevention programmes.

### Preventure

Preventure is a selective prevention programme and is one of the few school-based programmes with long-term effects on adolescents' drinking behaviour and binge drinking [16,19,20]. In research conducted in Canadian and English samples of adolescents, effects of the programme were found on abstinence, quantity and frequency of drinking, binge drinking, and problem drinking symptoms at four months and one year after the programme [16,19]. In addition to the effects on alcohol use, positive effects were found on emotional and behavioural problems, i.e. depression, panic attacks, truancy, and shoplifting [21].

The Preventure programme specifically targets young adolescents who have two well-known risk factors for heavy alcohol consumption: early-onset alcohol use [22,23] and personality risk for alcohol abuse (e.g. [24]). The programme is based on the theory that personality is an important construct for understanding adolescents' alcohol use and abuse. Two personality dimensions were previously found to be predictive of heavy alcohol use and alcohol use disorders, namely (1) an impulsive sensation seeking dimension, and (2) a behavioural inhibition dimension [16]. The first category involves young sensation seekers and young people with low impulse control, the second reflects a neurotic personality involving more anxious and negative thinking young people. Within these two dimensions, [name] and colleagues [16] distinguished four personality profiles at higher risk of developing alcohol problems: Sensation Seeking (SS), Impulsivity (IMP), Anxiety Sensitivity (AS) and Negative Thinking (NT).

The four personality profiles were subsequently found to be strongly related to adolescents' quantity and frequency of drinking, frequency of binge drinking, and severity of alcohol problems [25,26]. Each personality profile is associated with specific substance misuse patterns, maladaptive motives for use, and vulnerability to specific forms of co-morbid psychopathology in adolescents [27,28]. Impulsivity is related to an increased risk of the early onset of alcohol and drug problems [29]. Sensation seekers drink more [30], tend to drink in order to enhance euphoric (intoxicating) effects [28], and are more at risk of adverse drinking outcomes (e.g. [30]). Highly anxiety sensitive persons show increased levels of drinking [31], are more responsive to the anxiety-reducing effect of alcohol, and are more likely to use alcohol to cope with negative feelings [28]. Persons with high levels of hopelessness often have depression-specific motives for alcohol use [32] and usually drink to cope with negative feelings [16,28,33,34].

The Preventure programme screens a school population for pupils who already drink alcohol and, additionally, belong to one of the four high-risk personality profiles. The programme identifies and treats high-risk adolescents, with the aim of preventing or intervening early before the high-risk adolescents engage in risky behaviours and/or these behaviours become problematic. The selected pupils are offered a tailored intervention based on cognitive behaviour therapy (CBT) and motivational interviewing. Cognitive behavioural techniques are used to target maladaptive thinking and coping skill deficits, and motivational interviewing techniques are used to address motivation to take responsibility for one's problematic behaviours. Motivational interviewing has proven to be effective for alcohol- and drug-related behaviour, and CBT can lead to reduction in anxiety sensitivity, depressive cognitions, and impulsivity (e.g. [35,36]). The manualized intervention, developed by [name] and colleagues [35], provides personalized feedback and personality-specific cognitive-behavioural exercises designed to facilitate more adaptive coping. The focus is not on drinking (or drug use) per se but on risky ways of coping with personality, such as avoidance, distraction, and aggressive thinking, that may lead to substance misuse or other risky behaviour.

### Aims and hypotheses

In 2009, a project was started to develop and test Preventure in the Netherlands, where currently there is no selective school-based alcohol prevention available [37]. The main objective of this project is to study the effectiveness of Preventure on drinking behaviour of young adolescents in secondary education in the Netherlands. The effectiveness of the Dutch Preventure is being assessed by conducting a clustered randomized controlled trial (RCT), with two conditions (treatment and control arms). This is the first time that Preventure has been studied outside the setting where it was developed, England and Canada, to prove its effectiveness outside this setting.

The most relevant outcomes are percentage reductions in binge drinking (≥ five drinks on one occasion in the past four weeks), weekly drinking, and drinking-related problems after 2, 6, and 12 months. The main hypothesis is that high-risk students who receive the personality targeted intervention will score lower on these outcomes relative to those in the no-treatment control group. In addition, our secondary aim is to test the effects of the programme on emotional and behavioural problems (e.g. aggression, truancy, and shoplifting). Our hypothesis is that Preventure facilitates lower depression rates, lower anxiety rates, lower delinquent behaviour rates, less problem behaviour, and lower truancy.

## Methods/Design

### Study design and time frame

The Preventure study is a 1-year RCT with two arms, an intervention and a control condition, testing the prevention programme effects, at 2, 6, and 12 months after the intervention (see Figure 1). Randomization is carried out at school level. The intervention condition consists of two group sessions based on cognitive behaviour therapy and motivational interviewing. The control condition receives no further intervention (business as usual).

**Figure 1 F1:**
[figure not shown]
**Study design**.

The recruitment, inclusion, and randomization of the participants (schools and students) started in Spring 2009. The data collection started in 2010. The final follow-up measurement is planned for the end of 2011.

### Participants

#### Recruitment

A total of 100 schools were selected randomly from a list of all public secondary schools (N = 405) in four regions in the Netherlands (Zuid-Holland, Utrecht, Gelderland, Overijssel). Schools were invited to participate in the study, if the following inclusion criteria were met: 1. school had at least 600 students, 2. < 25% of students were from migrant populations, 3. school did not offer special education. A total of 15 schools were willing to participate and fulfilled the inclusion criteria. The main reasons for schools not participating were lack of time and no interest in participating in research in general.

#### Eligibility

Students were eligible to enter the trial if they fulfilled the following inclusion criteria: 1. life time prevalence of alcohol use (i.e. having drunk at least one glass of alcohol once in their life), 2. belonging to one of the four personality high-risk groups for (future) heavy drinking (AS, SS, NT or IMP) and 3. informed consent of the student and his or her parents. The study is aimed at students from 13 to 15 years of age. This is in contrast to [name] et al.'s study [16], in which students aged 14 to 17 were studied. The reason for this difference is the age of onset, which is lower among Dutch youngsters than among their study sample.

In order to select those students fulfilling the selection criteria, a screening survey among all students attending grade 8 and grade 9 of the 15 schools was carried out. The students who scored more than one standard deviation above the sample mean on one of the four personality risk scales (AS, SS, NT, or IMP) of the Substance Use Risk Profile Scale (SURPS) [25], were classified as belonging to a risk group for the development of alcohol problems. If a student scored high on more than one subscale, he or she was assigned to the personality group in which he or she showed the largest statistical deviation with respect to the z-scores.

#### Consent

Parents were informed of the study (screening and intervention) through a letter sent home from the schools asking them to contact the researchers by phone or e-mail if they did not wish their child to participate in the study (passive informed consent). Parents were told that the intervention was coping-skill training designed to reduce adolescent risk taking, with alcohol abuse as an example. To assure participants' confidentiality, parents were not explicitly informed about any of the selection variables of the study. On the day of the screening, students were given information on the screening, the ethical issues (confidentiality and the voluntary nature of participation), and the intervention. Parents and students provided active informed consent to participate in the intervention part of the study.

The study was evaluated by the Medical Ethical Commission for Mental Health (METIGG), which considered the study did not fall within the WMO Act (Medical Research Involving Human Subject Act). As a result no ethical approval was necessary. However, for the consent procedure, we adhered to the guidelines and advices of the METIGG.

#### Randomization

Randomization occurred at the school level to avoid contamination between conditions. An independent statistician assigned the participating schools randomly to one of the two conditions: intervention or control. Randomization was carried out using a randomization scheme, stratified by level of education and school size, with the schools as units of randomization.

### Sample size

#### Power

The power calculation reflects the idea that we want to induce a reduction in the percentage of students engaging in binge drinking (drinking five or more glasses of alcohol on one occasion) at least once during the last four weeks, from the current estimated 50% (among life-time users grade 9/10; estimate based on the results of a national school survey, [1]) to 35%. For a 15% reduction after 12 months among the students in grade 9/10, a sample size of N = 183 in each condition was required to test the hypothesis in a 2-sided test at alpha = 0.05 and a power of (1-beta) = 0.80. Because of the loss of power due to randomization of schools (and not students) and the increase in error because of applying a multiple imputation procedure to fill in missing values, 183*1.4 = 256 respondents per condition (intervention and control) needed to be included at baseline to test the effectiveness of the Dutch Preventure programme.

#### Number of students

According to the power analyses, a net sample of 256 respondents in each condition was needed. On the assumption of a 40% participation rate, 45% of respondents belonging to one of the risk groups (estimates based on [16,19]), a life time prevalence at baseline of 77%, and 93% of children present in the class at the data collection time (estimates based on [1]), a survey sample of N = 3,972 students was needed.

### Study intervention

To develop the Dutch Preventure programme, the principles and guidelines of the original Canada/UK programme were followed in collaboration with the original developers of Preventure.

#### Theoretical basis

Preventure incorporates the principles from motivational and cognitive behavioural therapy and is adapted to different personality profiles for substance abuse: anxiety sensitivity, negative thinking, sensation seeking, and impulsivity. The intervention is brief, as the literature strongly suggests that brief interventions can be very effective in changing drinking patterns and related problems. An effective component of successful brief interventions for alcohol abuse is the persuasiveness of individualized feedback. Therefore, Preventure provides pupils with personalized feedback on their results from a personality and motivational assessment. Preventure also includes cognitive behavioural skills training specifically relevant to each personality profile. The literature has shown that successful cognitive behavioural therapy can lead to reductions in anxiety sensitivity in anxiety patients, depressive cognitions in depressed patients, and impulsivity in adolescents with externalizing disorders [38,39,36].

The intervention consists of three main components: (1) psycho-education, (2) behavioural coping skills, and (3) cognitive coping skills [16]. In the coping skills sections, students are engaged in activities to induce automatic thoughts. Simultaneously, they are trained to use cognitive restructuring techniques to counter such thoughts. Cognitive restructuring training has been shown to have a positive impact on the reduction of alcohol and drug abuse and symptoms of psychological disorders [35].

#### Intervention condition

The intervention involved two group sessions, carried out at the participants' schools. The group sessions were adapted to one of the four personality profiles. This means that there were four different groups of two sessions each. Both group sessions lasted 90 minutes and were spread across two weeks. The intervention was provided by a qualified counsellor and a co-facilitator. The three counsellors and two co-facilitators had received two days training from [name], who developed the original intervention. Furthermore, all the counsellors had practiced the two group sessions at a pilot school with students who met the inclusion criteria (drinkers with high-risk personality profiles).

The intervention used student manuals. The original student manuals, developed in Canada, were translated and adapted to the cultural and school context of the Netherlands. The examples, the real-life stories, and the illustrations used in the programme manuals were adapted to the Dutch situation. The student manuals consist of text, exercises, and real-life experiences or scenarios. The real-life scenarios were generated by previously organized focus groups of high-risk personality adolescents. In four focus groups (one group for each personality risk factor), students were asked to share their own experiences regarding, for example, alcohol and drugs. The student manuals had been tested during the pilot sessions at the pilot school. Students were asked to give their opinion on the content, the illustrations, and real-life stories used in the manuals.

In the first group session, psycho-educational strategies were used to educate students about the target personality variable (NT, AS, IMP, or SS) and the associated problematic coping behaviours, such as interpersonal dependence, aggression, risky behaviours, and substance misuse. Students were motivated to explore their personality and ways of coping with their personality through a goal-setting exercise. Thereafter, they were introduced to the cognitive behavioural model by analysing a personal experience according to the physical, cognitive, and behavioural responses.

In the second session, participants were encouraged to identify and challenge personality-specific cognitive thoughts that lead to problematic behaviours. For example, the impulsivity intervention focused on not thinking things through and aggressive thinking, and the sensation-seeking intervention focused on challenging cognitive thoughts associated with reward seeking and boredom susceptibility.

#### Control condition

Students assigned to the control group received no further intervention. An inventory among the participating schools will reveal whether other specific substance use prevention programmes were being used, apart from the common lessons in the curriculum, e.g. biology classes.

### Data collection and instruments

The screening survey collected data by means of an online questionnaire on alcohol use, demographics, and personality risk factors. The data collection took place during a regular lesson (approximately 50 minutes), and questionnaires were administered by a research assistant from the Trimbos Institute. Those students randomly assigned to the experimental or control condition have completed, or will complete, the post-treatment survey after 2, 6, and 12 months. Data for the follow-up measurements have been, or will be, also collected online at school. The follow-up survey contains the same assessments as the screening survey. An overview of all measurements is given in Table 1.

**Table 1 T1:** Overview of measurements

Measurement	Baseline (screening)	Follow-up I (2 months after baseline)	Follow-up II (6 months after baseline)	Follow-up III (12 months after baseline)
Demographic characteristics	*	*	*	*
Truancy	*	*	*	*
Alcohol:				
Drinking behaviour	*	*	*	*
Drinking motives	*	*	*	*
Drinking problems	*	*	*	*
Perceived parental rules	*	*	*	*
Drinking parents	*	*	*	*
Tobacco:	*	*	*	*
Smoking behavior	*	*	*	*
Smoking parents	*	*	*	*
Perceived parental rules	*	*	*	*
Marijuana:	*	*	*	*
Marijuana-using behaviour	*	*	*	*
Marijuana parents	*	*	*	*
Other:	*	*	*	*
Personality	*	*	*	*
Anxiety	*	*	*	*
Psychological problems	*	*	*	*
Delinquency	*	*	*	*
Depression	*	*	*	*
Self control	*	*		

As already mentioned, the SURPS [25] distinguishes four personality profiles. Each profile is assessed using five to seven items that could be answered on a 4-point scale, 1 = *strongly disagree*, 2 = *disagree*, 3 = *agree*, 4 = *strongly agree*. The SURPS scale has 23 non-overlapping items that assist in discriminating personality dimensions independent of substance use behaviour. Negative Thinking (7 items) refers to hopelessness, which might lead to depressive symptoms. A sample item on the Negative Thinking subscale is 'I feel that I'm a failure.' The Anxiety Sensitivity dimension (5 items) measures fear of bodily sensations, and an example item is 'It frightens me when I feel my heart beat change.' The Sensation Seeking subscale (6 items) measures the tendency to seek out thrilling experiences, e.g. 'I would like to learn how to drive a motorcycle.' The tendency to act without thinking is measured by the Impulsivity subscale (5 items), and an example of this subscale is 'I often don't think things through before I speak.' Studies in both adolescent and adult samples in several countries, including the Netherlands, have shown that this scale has good internal reliability, good convergent and discriminant validity, and adequate test-retest reliability [34,40,41,25,27]. The instrument was translated into Dutch by an English speaking language consultant, has been successfully applied [34], and was tested at schools before use in the screening survey.

### Outcomes

When the data analysis takes place, the primary outcomes will be percentage reductions in binge drinking, weekly and weekend drinking, and drinking-related problems. To assess life-time alcohol use and binge drinking, two questions will be used that are widely used in school surveys, including the ESPAD study [2], Monitoring the Future [42], and the national school surveys in the Netherlands [1,43]. The average standard units in the last week will be assessed with the Weekly Recall [44,45]. Weekly and weekend alcohol use is defined by the quantity-frequency measure [46,47]. To assess behavioural symptoms of adolescent problem drinking, the Rutgers Alcohol Problems Index (RAPI) [48] will be used. The RAPI has been well validated for use with both clinical and community adolescent samples [49-51,48].

Other outcomes will include percentage reductions in depressive feelings, anxiety symptoms, problem behaviour, drinking motives, truancy, and delinquent behaviour. Depressive feelings will be measured with the widely used 20-item (Dutch version) of the Centre for Epidemiological Studies Depression Scale (CES-D) [52,53]. The Childhood Anxiety Sensitivity Index (CASI) [54] is a self-report questionnaire to assess children's and adolescents' fear of anxiety symptoms. The CASI has good internal consistency and acceptable 2-week test-retest reliability [55]. The Strengths and Difficulties Questionnaire (SDQ) [56] will be used as a behavioural screening instrument for early detection of psychological problems. The DMQ-R [57] is the most widely used instrument to assess drinking motives among young people. The DMQ-R has been well validated in several international (e.g. [58]) and national studies (e.g. [51]).

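### The anxiety hypothesis and outcome do not match the only anxiety instrument named, which measures anxiety sensitivity rather than anxiety symptoms or rates

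*Protocol article*

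**What the plan says.** Three places in the protocol article bear on this point.

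- **Hypothesis** (Aims and hypotheses): "Our hypothesis is that Preventure facilitates lower depression rates, lower anxiety rates, lower delinquent behaviour rates", followed by problem behaviour and truancy.
- **Outcome** (Outcomes): "Other outcomes will include percentage reductions in depressive feelings, anxiety symptoms, problem behaviour", followed by drinking motives, truancy and delinquency.
- **Instrument** (Outcomes): the CASI "is a self-report questionnaire to assess children's and adolescents' fear of anxiety symptoms".

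The other instrument that might touch on anxiety is the Strengths and Difficulties Questionnaire (SDQ), which "will be used as a behavioural screening instrument for early detection of psychological problems". Table 1 has separate rows for anxiety and for psychological problems, each marked at baseline and at all three follow-ups, without naming the scales.

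Elsewhere the article treats anxiety sensitivity as a personality trait. It is one of the four profiles on which students were selected (Eligibility). On the selection scale, the SURPS, "The Anxiety Sensitivity dimension (5 items) measures fear of bodily sensations" (Data collection and instruments). Under Theoretical basis the programme "is adapted to different personality profiles for substance abuse: anxiety sensitivity, negative thinking, sensation seeking, and impulsivity".

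**The concern.** The hypothesis concerns anxiety rates, the outcome concerns anxiety symptoms, and the instrument measures fear of those symptoms. A student can be very afraid of a racing heart and seldom have one, or have frequent symptoms and fear them little. A difference on the CASI therefore does not answer the question the hypothesis asks.

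What is at stake is how one secondary result will be interpreted. The Preventure section of the Background cites earlier positive effects on depression and panic attacks, and effects on emotional and behavioural problems are the trial's secondary aim. If a CASI result carries the label anxiety symptoms, a reader may take it as confirming, or failing to confirm, an effect on anxiety itself. Neither reading would be supported by that scale.

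**Working it through.** No arithmetic applies to the construct mismatch. The article gives no effect size, standard deviation, event rate, cut-off or power for the anxiety outcome. The check is to compare the statements.

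**1. Label against instrument.**

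| Element | Where | Construct |
|---|---|---|
| Hypothesis | Aims and hypotheses | level or frequency of anxiety ("lower anxiety rates") |
| Outcome | Outcomes | anxiety symptoms |
| Instrument | Outcomes | "fear of anxiety symptoms" |

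The first two rows can be reconciled if rates is read loosely. The third cannot be reconciled with either. The instrument's own name and the article's one-line description are enough to show this.

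**2. Is the CASI meant as the measure of anxiety symptoms?** The article does not say so in one sentence. The link is inferred: the CASI description comes straight after the depression scale, in the order in which the outcomes are listed, and no other instrument is described as concerning anxiety.

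**3. Could the SDQ fill the gap?** As described, it screens for psychological problems, and Table 1 keeps that row apart from the anxiety row. The article does not assign it to anxiety symptoms.

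**4. Comparison with depression.** For depression, the selection trait (negative thinking, on the SURPS) and the outcome (depressive feelings, on the CES-D) are different constructs with different scales. For anxiety, the selection trait is anxiety sensitivity and the named outcome scale also measures anxiety sensitivity. The separation made for depression is absent for anxiety.

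**5. Baseline adjustment.** Statistical Analyses fixes sex, age and educational level as covariates and adds possible confounders after a balance check. The baseline value of the outcome is not among the fixed covariates, although Table 1 shows anxiety measured at baseline.

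**6. Reach.** The only design calculation is for binge drinking, 50% against 35%, two-sided alpha 0.05, power 0.80. The two-proportion formula with continuity correction gives 183 per condition, as stated (170 without the correction), and 183 × 1.4 = 256.2, stated as 256. Anxiety does not enter this calculation, so the sample size is untouched.

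**The case against.** The strongest reply is that this is a terminology slip in a condensed article. The scale is named in full and its construct is disclosed in the same section, so nothing is hidden. The list of instruments is evidently incomplete, since truancy and delinquency are outcomes with no instrument named. The full protocol or questionnaire may contain a symptom measure. The word rates is also used loosely: depression rates are hypothesised while depression is measured with a 20-item scale.

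Much of this stands. The loose use of rates is general and not a fault specific to anxiety. That a symptom measure may exist elsewhere is a fair caution. But this is more than a detail left to a fuller document: the article states the hypothesis, the outcome and an instrument, and they do not fit together.

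Three stronger readings may tempt a reader, and the article does not support them.

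- **That regression to the mean distorts the result.** Students in the anxiety-sensitivity group were selected for high scores on a scale that appears related, so their CASI scores may fall by follow-up. The same screening rule was applied in both arms, and Statistical Analyses compares the intervention condition with the control condition. The expected fall is common to both arms and drops out. It would matter only if percentage reduction were read as an uncontrolled change from baseline, and no such analysis is described.
- **That the CASI would show only movement in the trait being treated.** Anxiety sensitivity is the assigned profile and session focus for one of the four groups. For the other three it is neither. The CASI is also not the scale used for selection.
- **That the trial cannot say anything about anxiety.** The article supports only the narrower statement that no instrument it names is described as measuring anxiety symptoms or rates.

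**Conclusion.** The point holds as a mismatch between label and instrument. A CASI difference would support a conclusion about anxiety sensitivity, and none about anxiety symptoms or rates. It affects one secondary hypothesis and is minor in scale. The primary drinking outcomes, the sample size and the validity of the between-arm comparison are unaffected.

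Two assumptions carry this. The first is that the CASI is the intended measure for the anxiety outcome, which follows from the order of the text and the lack of any other anxiety scale but is not stated outright. The second is that the anxiety row of Table 1 refers to the CASI, so that a baseline score exists. If the SDQ or another collected measure was meant for anxiety symptoms, the mismatch is resolved by saying so. The protocol states a hypothesis and no conclusion, so the fault lies in what the plan sets up to be claimed.

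**What to change.** 1. In Aims and hypotheses and in Outcomes, rename the anxiety hypothesis and outcome as anxiety sensitivity (CASI), and state that no conclusion on anxiety symptoms or rates will be drawn from it.
2. Alternatively, if another measure already collected, such as SDQ items, is meant to cover anxiety symptoms, name it for that outcome and keep the CASI as a separate outcome under its own name.
3. In Statistical Analyses, add the baseline CASI score as a covariate in the between-arm CASI comparison, alongside sex, age and educational level. This is for precision; it does not cure the mismatch. The gain depends on the correlation between baseline and follow-up scores, which the article does not give.

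The cost is a change of wording and one covariate. No new instrument or data are needed, so it remains feasible although data collection started in 2010. The downside is a narrower secondary claim.
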